## Appendix 2: ALSFRS-R Rating Scale

Svensk version av ALSFRS-R Poäng 4-3-2-1-0; 4 bäst, 0 sämst funktion

1. Tal

Normal talprocess

Möjligen talproblem

Begripligt vid upprepning

Tal kombinerat med icke röstkommunikation

Förlust av användbart tal

1. Salivation

Normal

Lindrig men definitivt överdrivet med saliv i munnen, kan ha nattlig dräggling

Måttlig överdriven saliv, kan ha minimal dräggling

Utmärkande överdriven salivation med en del dräggling

Utmärkande dräggling; behov av konstant pappers- eller tygnäsduk

1. Sväljning

Normal matvana

Tidig ätproblematik- tillfälligt svälja fel och storkna

Konsistensförändring av maten

Behov av tillägg med sondmatning

Fullständig parenteral eller enteral matning

1. Handskrift

Normal

Sakta eller slarvig; alla ord är läsliga

Alla ord är inte läsliga

Kan greppa en penna men kan inte skriva

Kan inte greppa en penna

- 1. Skära mat och använda matredskap (patienter utan stomi)

Normal

Lite långsam och klumpig, men behöver inte hjälp

Kan skära det mesta av maten, men klumpigt och långsamt; lite hjälpbehov

Maten måste skäras av någon, men kan äta långsamt

Behöver matas

- 1. Skära mat och använda matredskap (patienter som har stomi)

Normal

Klumpig men kan genomföra alla manipulationer självständigt

En del hjälpbehov med tillslutning och med fästanordning

Ger minimal assistens till vårdgivare

Oförmögen att utföra någon del av arbetsuppgiften

1. På/avklädnad och hygien

Normal funktion

Oberoende och fullständig självhjälp med kraftansträngning eller avtagande effektivitet/skicklighet

Återkommande assistens eller ersättande metoder

Behov av närvarande vid självhjälp

Totalt beroende

1. Vändning i sängen och justering av sängkläder

Normal

Något långsam och klumpig, men inte behov av hjälp

Kan vända sig själv eller justera lakanet, men med stora svårigheter

Kan initiera men inte vända sig eller justera lakan själv

Hjälplös

1. Gång

Normal

Lätta förflyttningssvårigheter

Gå med assistens

Ingen egen förflyttningsfunktion

Ingen meningsfull benfunktion

1. Gå i trappa

Normal

Långsam

Lätt ostadighet eller trötthet

Behov av assistens

Kan inte göra det

1. Dyspné

Ingen

Förekommer vid gång

Förekommer vid en eller flera av följande: äta, bada, på/avklädnad (ADL)

Förekommer vid vila, svårighet med andning vid sittande eller liggande

Betydelsefull svårighet, med övervägning om användning av mekaniskt respiratoriskt stöd

1. Ortopné

Ingen

En del svårigheter under sömn på natten med otillräckliga andetag. Använder inte rutinmässigt mer än två kuddar

Behöver extrakuddar för att kunna sova

Kan endast sova sittande

Kan inte sova utan mekanisk ventilation

1. Respiratorisk insufficiens

Ingen

Intermittent användning av BiPAP

Kontinuerlig användning av BiPAP under natten

Kontinuerlig användning av BiPAP under dagen och natten

Invasiv mekanisk ventilation genom intubation eller tracheostomi

Hur många år är det sedan första symtom? År:________ Totalpoäng:__________

## Appendix 3: Norris Rating Scale

**ALS**

1. Hålla upp huvudet 3=Normal, 2=Nedsatt, 2=svag, 0=saknas
2. Tugga mat
3. Svälja
4. Tala
5. Vända sig i sängen
6. Sitta upp
7. Tömma tarmen/blåsan
8. Andas
9. Hosta
10. Skriva sitt namn
11. Knäppa knappar/blixtlås
12. Äta själv
13. Resa sig upp själv
14. Lyfta bok eller bricka
15. Lyfta gaffel, penna
16. Ändra läge av arm
17. Gå i trappor, en våning
18. Gå ett kvarter
19. Gå över rummet
20. Gå med assistans
21. Stå upp
22. Ändra läge av ben
23. Armreflexer Normal=3, Hyper/Hypo=2 Saknas=1, Klonus=0
24. Benreflexer
25. Masseterreflex Saknas=3, Finns=2 Hyper=1, Klonus=0
26. Babinski höger Flexion=3 Ingen rörelse=2 Odeciderad = 1, Extension= 0
27. Babinski vänster
28. Fascikulationer Inga =3, Lätta= 2 Måttligt = 1, Uttalade = 0
29. Atrofier: ansikte, tunga
30. Atrofier: armar, skuldror
31. Atrofier, ben, höfter
32. Emotionellt labil
33. Uttröttbarhet Ingen eller lätt = 2 Måttlig eller uttalad = 0
34. Rigiditet i benen

Summa________________ (Max 100)

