## Rationale for study design and dose

The design of the study is based on the aim to study safety, tolerability and efficacy of ILB solution in patients with ALS. Doses up to 24 mg/kg ILB has been administered to 79 healthy volunteers, but as ILB has never been administered to ALS patients and never more than two subsequent injections, a careful approach with low (1 mg/kg) and few doses (5 injections) with 1-week dosing interval has been chosen. The combined safety data from nonclinical and clinical studies indicate that the proposed dose can be administered without any safety concerns.

No control group is used as there are no spontaneous remissions or recovery of the disease. The progression of the disease is linear in the two clinical rating scales used, and therefore the rating of disease progression is reliable and standard in ALS research.

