## Efficacy endpoints

### Functional rating with ALSFRS-R and Norris scales

Both these scales will be reported according to the manuals with changes from baseline using summary statistics.

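### The Norris key printed at item 1, which by layout governs items 1 to 22, scores both impaired and weak as 2 and has no 1; it is very probably a misprint, and it distorts change from baseline if followed

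*Protocol*

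**What the plan says.** Section 20.3 (Appendix 3) prints the Norris form with 34 items and a stated maximum of 100. Item 1 carries the key "3=Normal, 2=Nedsatt, 2=svag, 0=saknas", that is normal, impaired, weak, absent. Items 2 to 22 carry no key of their own; item 22 reads only "Ändra läge av ben". The next key is at item 23: "Armreflexer Normal=3, Hyper/Hypo=2 Saknas=1, Klonus=0". Further keys follow at item 25, "Masseterreflex Saknas=3, Finns=2 Hyper=1, Klonus=0", at item 26, "Babinski höger Flexion=3 Ingen rörelse=2 Odeciderad = 1, Extension= 0", at item 28 (none 3, slight 2, moderate 1, marked 0) and at item 33 (2 or 0).

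Section 11.4.1 has the Investigator rate disease severity with the forms in Appendices 2 and 3. Table 2 schedules this at Visit 1a and at Visits 2 to 9. Section 7.2 lists the Norris rating as a secondary endpoint. Section 16.6.1 gives the analysis: "Both these scales will be reported according to the manuals with changes from baseline using summary statistics". The manuals are not reproduced in the protocol.

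**The concern.** An ordered four-category key needs four distinct scores. Here two adjacent categories share the score 2, and the step to the last category is two points wide. A rater who follows the form cannot show a change between impaired and weak on these items, and shows a change between weak and absent at double weight. A rater who notices the slip, or works from a manual with a different key, will score 1 for weak. The protocol does not say whether form or manual governs the rater.

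The analysis stage cannot repair this. The information is fixed when the item is rated, and if only the number 2 was kept, no later rule can tell the two categories apart. At stake is the change from baseline on a named secondary efficacy endpoint. The same scale also enters the optional interim look in Section 16.7 through disease severity, which Section 11.4.1 defines as ALSFRS-R and Norris.

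**Working it through.** **Inputs.** All come from Appendix 3: the printed keys, their positions (items 1, 23, 25, 26, 28 and 33) and the stated maximum of 100.

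**Step 1: how far the item 1 key reaches.** Carry each key down to the next printed key and add the top scores.

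- Items 1-22: 22 × 3 = 66
- Items 23-32: 10 × 3 = 30
- Items 33-34: 2 × 2 = 4
- Total: 66 + 30 + 4 = 100

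This reproduces the stated maximum exactly. Had item 32 fallen under the 2/0 key, the total would be 99. The carry-down reading is therefore well supported. The sum depends on top scores only, however, so it neither reveals nor tests the fault in the middle of the key.

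**Step 2: compare the four-level keys.**

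| Items | Scores, best to worst |
|---|---|
| 1-22 | 3, 2, 2, 0 |
| 23-24 | 3, 2, 1, 0 |
| 25 | 3, 2, 1, 0 |
| 26-27 | 3, 2, 1, 0 |
| 28-32 | 3, 2, 1, 0 |

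Only the first departs from the pattern, and the missing value is 1.

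**Step 3: effect per item.**

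| Change in one item | Printed key | If weak scores 1 |
|---|---|---|
| Normal to impaired | -1 | -1 |
| Impaired to weak | 0 | -1 |
| Weak to absent | -2 | -1 |
| Normal to absent | -3 | -3 |

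Improvements are the same with the sign reversed.

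**Step 4: effect on the total.** Let S be the number of items among 1-22 rated weak at a visit. The two keys differ only in that category, and by 1 point, so

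printed total - total with weak as 1 = S

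printed change - change with weak as 1 = S(visit) - S(baseline)

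If three items go from impaired to weak, the printed change is 0 instead of -3. If three items go from weak to absent, it is 3 × (-2) = -6 instead of -3. If one item does each, S is unchanged and both keys give -2.

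**Step 5: the ceiling.** S lies between 0 and 22. With all 22 items weak, the subtotal is 22 × 2 = 44 as printed and 22 × 1 = 22 with weak as 1. The distortion in change from baseline is therefore at most 22 points in either direction, reached only if all 22 items move into, or out of, the weak category.

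**The case against.** The strongest reply is that this is an obvious slip of one digit. The pattern elsewhere on the form makes the intended value plain, and Section 16.6.1 says reporting follows the manuals. The study has one centre, the Investigator does the rating, and inclusion criterion 5 requires Norris ratings before dosing, so the scale was already in use and may have been scored correctly throughout. Data go into an electronic CRF (Section 15.2), and nothing shows that it carries this key. Much of this stands: how scores are actually recorded is unknown. It does not cure the error, because Section 11.4.1 sends the rater to this appendix, and a manual with a different key would leave two rules in conflict.

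A reader might infer three stronger things that the protocol does not support.

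- *The error hides decline.* Step 4 shows that it can mask or exaggerate decline, and can mask or exaggerate improvement. The net direction depends on how many items enter and leave the weak category, and the protocol gives no such figures.
- *It undermines the single-arm design.* Section 8.2 does state "The progression of the disease is linear in the two clinical rating scales used", and a 3-2-2-0 key has unequal steps. But that section first rests the lack of a control group on the absence of spontaneous remission or recovery, and ALSFRS-R, the other scale, is unaffected.
- *22 items × 9 rating visits × 15 patients = 2,970 scores are wrong.* That product counts every rating made under this key with complete attendance. Only ratings of weak are affected, and only where the printed key was used.

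Also, the lack of a 1 is a fault of the item 1 key, not of the whole form: items 23 to 32 do have it.

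**Conclusion.** The key for items 1 to 22 is wrong as written and should be fixed. It is the scoring rule for 22 of 34 items and 66 of 100 points on a named secondary endpoint. As printed, it merges two impairment levels and doubles the step from weak to absent. The distortion in a patient's change from baseline equals the change in the number of items rated weak: 22 points at the very most, in a direction that cannot be stated in advance.

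This rests on two assumptions. The item 1 key is taken to apply down to item 22, which the layout implies and the total of 100 supports. Weak is taken to be meant as 1, which the other keys make very probable but only the manual can confirm. Whether any recorded score is affected depends on which key the raters used. The grade is should-fix, not must-fix, because the endpoint is secondary and summarised descriptively, and the primary safety endpoints are untouched.

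**What to change.** 1. Reconcile the item 1 key with the Norris manual so that items 1 to 22 have four distinct scores (3-2-1-0, as elsewhere on the form). Correct Appendix 3, the rating form and, if it carries the same key, the electronic CRF.
2. For patients already rated, establish which key was used and re-derive item scores from the recorded verbal category.
3. Where only a 2 was recorded and the category cannot be recovered, flag the item and report the Norris total twice: once with all ambiguous items as 2 and once with all as 1. Do not drop the items, because totals would then rest on different items across patients and visits and would no longer be out of 100. These two totals bound the score at each visit. They do not by themselves bound the change, since an item ambiguous at both baseline and a later visit cancels under either choice; the number of such items should be stated.

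The cost is a one-digit correction, a check of form and CRF against the manual, and a data query for patients already rated. It should be done before any interim or final summary of the scale.

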## Appendix 4: Livskvalitet - försöksperson

**Livskvalitet - Försöksperson/Närstående: Egentestning**

Skattning av välbefinnande

Uppskatta **ditt** välbefinnande genom att sätta ett lodrätt streck på linjen där du tycker att det passar bäst in på dig just nu. Linjen sträcker sig från mycket dåligt till mycket bra.

Datum_____________ Försöksperson/Närstående______________

Hur skattar du ditt allmänna välbefinnande?

Mycket dåligt ­­­_____­_____________________________________________ Mycket bra

mm:__ __ __

Hur skattar du ditt fysiska välbefinnande?

Mycket dåligt ­­­_____­_____________________________________________ Mycket bra

mm:__ __ __

Hur skattar du ditt psykiska välbefinnande?

Mycket dåligt ­­­_____­_____________________________________________ Mycket bra

mm:__ __ __

## Appendix 5: Livskvalitet - närstående

**Livskvalitet - Närstående/Närstående**

Skattning av välbefinnande

Uppskatta **din närståendes** välbefinnande genom att sätta ett kryss på linjen där du tycker att det passar bäst in på honom/henne just nu. Linjen sträcker sig från mycket dåligt till mycket bra.

Datum______________ Försöksperson / Närstående_________________

Hur skattar du din närståendes allmänna välbefinnande?

Mycket dåligt ­­­_____­_____________________________________________ Mycket bra

mm:__ __ __

Hur skattar du din närståendes fysiska välbefinnande?

Mycket dåligt ­­­_____­_____________________________________________ Mycket bra

mm:__ __ __

Hur skattar du din närståendes psykiska välbefinnande?

Mycket dåligt ­­­_____­_____________________________________________ Mycket bra

mm:__ __ __

## Appendix 6: Autonoma och sensoriska symtom

0= ej; 1=Något; 2 = Måttligt; 3=Mycket

Autonoma och sensoriska symtom

| **Visit** | **1a** | **2** | **3** | **4** | **5** | **6** | **7** | **8** | **9** |
| --- | --- | --- | --- | --- | --- | --- | --- | --- | --- |
|  | Screening | Dosing | Dosing | Dosing | Dosing | Dosing | Follow-up | Follow-up | End of study follow-up |
| **Day** | -30 to -7 | 1 | 8 | 15 | 22 | 29 | 36 | 50 | 99 |
| **Time window** | ±3 | ±3 | ±3 | ±3 | ±3 | ±3 | ±3 | ±7 | ±7 |
| Smärta |  |  |  |  |  |  |  |  |  |
| Parestesier |  |  |  |  |  |  |  |  |  |
| Frusenhet |  |  |  |  |  |  |  |  |  |
| Svettningar |  |  |  |  |  |  |  |  |  |
| Obstipation |  |  |  |  |  |  |  |  |  |
| Frekvent avföring |  |  |  |  |  |  |  |  |  |
| Miktionssvårigheter |  |  |  |  |  |  |  |  |  |
| Frekventa miktioner |  |  |  |  |  |  |  |  |  |
| Domningar |  |  |  |  |  |  |  |  |  |
| Yrsel |  |  |  |  |  |  |  |  |  |
| Trötthet |  |  |  |  |  |  |  |  |  |
| Uttröttbarhet |  |  |  |  |  |  |  |  |  |
| Insomningsproblem |  |  |  |  |  |  |  |  |  |
| Frekventa uppvaknanden |  |  |  |  |  |  |  |  |  |
| Hjärtklappning |  |  |  |  |  |  |  |  |  |
| Oregelbunden hjärtrytm |  |  |  |  |  |  |  |  |  |

